### Sample size calculation

2.3

This trial has two prespecified primary endpoints: change in Insomnia Severity Index (ISI) score and change in task-evoked prefrontal oxygenated hemoglobin (Oxy-Hb) response measured by fNIRS. A Bonferroni-style alpha-allocation strategy will be used to control the family-wise type I error rate, with a two-sided alpha of 0.025 assigned to each primary endpoint. For the ISI endpoint, a 3-point between-group difference was considered clinically meaningful, consistent with the lower bound of minimal clinically important difference estimates for the ISI (32), and supported by a randomized acupuncture trial in primary insomnia (33). Using a pooled SD of 3.8 from a comparable insomnia population (33), the standardized effect size was estimated as Cohen’s *d* = 3.0/3.8 = 0.79. With a two-sided *α* of 0.025, 1:1 allocation, and 80% power, approximately 32 participants per group are required.

For the fNIRS endpoint, a standardized effect size of *d* = 0.80 was assumed for the between-group difference in prefrontal Oxy-Hb change. With alpha = 0.025, 1:1 allocation, and 80% power, approximately 27 participants per group are required. Because the ISI endpoint requires the larger analyzable sample, it is the binding constraint. After allowing for a 20% attrition rate, the required enrollment sample size was calculated as follows:

$$n_{\text{enrolled}}=\frac{n_{\text{required}}}{1-\text{attrition rate}}=\frac{32}{1-0.20}=40$$

Thus, 40 participants per group, for a total of 80 participants, will be randomized.

Sensitivity analysis showed that, with 32 analyzable participants per group, the study would retain approximately 80.4% power for ISI and 81.4% power for fNIRS Oxy-Hb at alpha = 0.025. If the true fNIRS effect decreases to *d* = 0.75, power would decrease to approximately 75.7%, indicating that the fNIRS endpoint is more sensitive to effect-size assumptions. Strict fNIRS acquisition, preprocessing, and quality-control procedures will therefore be implemented. Previous fNIRS acupuncture studies have generally included 12–20 participants (34–36). On this basis, at least 20 participants per group will be included in the fNIRS analysis. After allowing for an anticipated dropout rate of 20%, 24 healthy controls per group will be planned for fNIRS assessment.

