### Data analysis

2.11

All statistical analyses will be performed by an independent statistician using SPSS version 29.0 (IBM Corp., Armonk, NY, USA) and R software (version 4.3.x). The primary analysis will follow the intention-to-treat principle, including all randomized participants; per-protocol analysis will be used as sensitivity analysis. Continuous variables will be summarized as mean ± SD or median (IQR), and categorical variables as counts and percentages. Baseline characteristics will be summarized descriptively, with standardized mean differences used to assess group balance. No formal baseline hypothesis testing will be performed. Baseline fNIRS comparisons between patients with CID and healthy controls will use ANCOVA controlling for age, sex, BMI, caffeine/alcohol intake, and recording time.

Longitudinal continuous outcomes will be analyzed using linear mixed-effects models with fixed effects for group, time, and group-by-time interaction, and a random intercept for each participant. The main treatment effect will be the between-group difference in change from baseline to week 4; week 8 will be analyzed as follow-up. An unstructured covariance matrix will be attempted first; if convergence fails, AR(1) or compound symmetry structures will be considered based on model fit. Missing data will be handled under the missing-at-random assumption using multiple imputation by chained equations with 20 datasets. The imputation model will include treatment group, time, baseline and available follow-up values, and relevant variables such as age, sex, ISI, PSQI, and HAMA. Results will be pooled using Rubin’s rules.

This is a superiority trial. For ISI, the null hypothesis is no between-group difference in change from baseline to week 4; the alternative is greater improvement in the treatment group. A 3-point ISI difference will be used for sample-size estimation and clinical interpretation but not as a noninferiority or superiority margin. Because there are two primary endpoints, a two-sided Bonferroni-adjusted alpha of 0.025 will be used for each. Secondary outcomes and exploratory fNIRS endpoints will be adjusted using the false discovery rate method where appropriate.

Raw fNIRS data will be processed using NirMaster software (Znion, Wuhan, China). To ensure transparency and reproducibility, the data analysis pipeline will follow standard fNIRS processing procedures, structured into preprocessing, quality control, and feature extraction.

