Data Preprocessing: First, the raw light intensity data will be converted to optical density (OD). Second, motion artifacts will be identified and corrected using spline interpolation. Third, a band-pass filter (0.01–0.1 Hz) will be applied to the OD data to reduce physiological noise (e.g., heartbeat, respiration) and low-frequency signal drift. Finally, the filtered OD data will be converted to relative concentration changes in oxy-Hb, deoxyhemoglobin (deoxy-Hb), and total hemoglobin (tHb) using the modified Beer–Lambert law. The differential pathlength factor (DPF) will be set to 6.0 for both 690 nm and 830 nm wavelengths.

Quality Control: Channel signal quality will be evaluated using the coefficient of variation (CV), which will be calculated based on the raw light intensity during the initial resting period. Channels with a CV > 15% will be considered to have excessive noise and will be excluded from further analyses (44). Participants with more than 20% of their channels categorized as low-quality will be entirely removed from the group-level fNIRS analysis.

Feature Extraction: In accordance with standard practices, oxy-Hb will serve as the primary indicator of cortical activation due to its higher sensitivity to task-related changes (45). To quantify task-evoked activation during the VFT, a GLM will be applied at the individual level. The design matrix will include the task conditions convoluted with a canonical hemodynamic response function (cHRF). Task-related regression coefficients (*β* values) will be extracted to represent the activation strength for each channel. For region-of-interest (ROI) analyses, the extracted *β* values from channels located within the bilateral dorsolateral prefrontal cortex (DLPFC) and medial prefrontal cortex (mPFC) will be averaged.

Longitudinal comparisons of ROI metrics (baseline, week 4, and week 8) will be conducted using independent-samples *t*-tests or Mann–Whitney *U* tests for comparisons between groups at each time point, with FDR correction applied to multiple fNIRS comparisons.

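### The fNIRS co-primary endpoint is given two incompatible analyses, so its 0.025 alpha and 81.4% power are not assured

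*Protocol article*

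**What the plan says.** Section 2.3 (Sample size calculation) names two primary endpoints, the second being "change in task-evoked prefrontal oxygenated hemoglobin (Oxy-Hb) response measured by fNIRS". It promises that "A Bonferroni-style alpha-allocation strategy will be used to control the family-wise type I error rate". Each of the two receives 0.025, two-sided.

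Section 2.11 (Data analysis) then gives two sets of instructions.

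- **General paragraphs.** Longitudinal continuous outcomes are analysed with "linear mixed-effects models with fixed effects for group, time, and group-by-time interaction, and a random intercept for each participant". The main effect is the group difference in change from baseline to week 4, and week 8 is follow-up. For the two primary endpoints, "a two-sided Bonferroni-adjusted alpha of 0.025 will be used for each". FDR is mentioned only for secondary outcomes and exploratory fNIRS endpoints. On baseline: "No formal baseline hypothesis testing will be performed".
- **fNIRS paragraphs.** Task-evoked activation is a GLM beta per channel. For the ROI analyses, betas from "channels located within the bilateral dorsolateral prefrontal cortex (DLPFC) and medial prefrontal cortex (mPFC) will be averaged". The ROI metrics at baseline, week 4 and week 8 are then compared by independent-samples t-test or Mann-Whitney test, as "comparisons between groups at each time point, with FDR correction applied to multiple fNIRS comparisons".

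**The concern.** The averaged prefrontal betas are the only task-evoked prefrontal Oxy-Hb summary that the protocol defines, so the last fNIRS sentence falls on the primary variable. It is not limited to exploratory use. An analyst can thus follow either set of instructions and claim to be on protocol.

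Two things are at stake. The first is the alpha split, because an FDR procedure over several tests is not a single test at 0.025. The second is the power statement, because the effect size in section 2.3 is defined on change and does not carry over to a comparison of levels at one visit. The choice between the two routes could be made after the data are seen, and it could decide whether a co-primary endpoint is met.

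**Working it through.** **1. The two instructions side by side**

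| | General paragraphs of 2.11, with 2.3 | fNIRS paragraphs of 2.11 |
|---|---|---|
| Quantity | Group difference in change to week 4 | Group difference in level at each visit |
| Visits tested | Week 4 is the main effect, week 8 follow-up | Baseline, week 4, week 8 |
| Test | Mixed model | t-test or Mann-Whitney |
| Error criterion | Two-sided 0.025, family-wise | FDR, level not stated |
| Baseline test between groups | None | Included |

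**2. The plan's own figures**

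Alpha: 0.025 + 0.025 = 0.05, so the Bonferroni split is valid.

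fNIRS power from a two-sample t-test with 32 per group and d = 0.80 on change: df = 62, noncentrality = d × √(n/2) = 0.80 × √16 = 3.2, two-sided alpha 0.025. The result is 81.4%, as stated. At d = 0.75 it is 75.7%, also as stated. The stated power is thus that of one test on change at 0.025.

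**3. Type I error of the fNIRS part under each reading**

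This was simulated with 40,000 null trials per scenario, 32 per arm, three visits and complete data.

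Assumptions not in the protocol: between-visit correlation 0.3 to 0.7; one to three ROI scores (the averaging sentence allows any of these) with correlation 0.5; the Benjamini-Hochberg procedure; FDR level q of 0.05 or 0.025. The mixed-model contrast is approximated by a t-test on change scores.

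| What counts as fNIRS success | q = 0.05 | q = 0.025 |
|---|---|---|
| Change to week 4 only, at 0.025 | about 2.5% | about 2.5% |
| Any rejection in the visit-wise set | 4.2–5.0% | 2.1–2.6% |
| Either analysis | 6.3–6.8% | 4.4–4.8% |

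The first row does not depend on q. A rejection at week 4 within the visit-wise set has probability about 1.5–2.5% at q = 0.05.

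These are global-null figures. FDR does not cap the family-wise error once some effects are real. With three visit-wise tests at q = 0.05, one real effect that is rejected at another visit raises the week-4 threshold to (2/3) × 0.05 = 0.033, above 0.025.

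**4. Does the planned power carry over?**

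Assume equal variances and no expected baseline difference. The SD of change is then √(2(1 − ρ)) times the SD at one visit, so d = 0.80 on change corresponds to a week-4 level difference of 0.80 × √(2(1 − ρ)).

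| ρ (assumed) | Week-4 d | Power at alpha 0.025, 32 per group |
|---|---|---|
| 0.3 | 0.80 × √1.4 = 0.95 | 93% |
| 0.5 | 0.80 × √1.0 = 0.80 | 81% |
| 0.7 | 0.80 × √0.6 = 0.62 | 57% |

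The level comparison matches the stated power only at a correlation near 0.5.

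**The case against.** The strongest reply is that the two parts can be read together. The general paragraphs fix 0.025 for each primary endpoint, name change to week 4 as the main effect, and confine FDR to secondary and exploratory fNIRS endpoints. If the visit-wise ROI tests are that exploratory layer, family-wise control holds. This reading is possible, but the fNIRS paragraph does not state it and does not set the primary variable apart.

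A reader might infer that error control fails outright and that the trial-level error is about 7%. The documents do not support that. The figure needs an FDR level of 0.05, which is not stated, and it needs a baseline or week-8 rejection to count as meeting the primary endpoint, which no section says. At q = 0.025, or counting week 4 only at q = 0.05, the visit-wise set shows essentially no excess under the global null.

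A reader might also infer that visit-wise tests are biased for the treatment effect. Under randomisation the expected baseline difference is zero, so the week-4 difference and the difference in change have the same expectation. What changes is precision, in either direction.

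The baseline clash is the smallest part. The no-testing rule follows the sentence on baseline characteristics, and the planned baseline comparison with healthy controls is a separate matter. That comparison cannot explain the listed baseline visit, however: it is assigned to ANCOVA, and healthy controls have no week-4 or week-8 data.

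**Conclusion.** The contradiction is in the text and concerns a co-primary endpoint. The stated family-wise control and the 81.4% fNIRS power are not assured, because both hold only if the mixed-model change contrast at 0.025 is the sole confirmatory fNIRS test.

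Under the global null, the visit-wise set ranges from no excess over the allotted 2.5% to about double it, depending on the FDR level and on which visits count. If either analysis could succeed, the excess is present at both FDR levels examined. These sizes rest on the assumed q, correlations and number of ROI scores; the conflict itself rests on none of them.

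**What to change.** State one confirmatory fNIRS test in section 2.11: one prespecified prefrontal summary (for example the mean beta over the pooled DLPFC and mPFC channels), the between-group difference in change from baseline to week 4, from the mixed model already described, at two-sided alpha 0.025. Label the per-visit, single-ROI, week-8 and connectivity comparisons under FDR as exploratory, and give the FDR level. Delete the between-group baseline test of ROI metrics; the healthy-control comparison is unaffected.

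Keep the 0.025/0.025 Bonferroni split. It is valid and matches the sample size, and a different multiplicity procedure is not needed to resolve this point.

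With this wording, the simulated fNIRS type I error is 2.4–2.6%, in line with the allotted 2.5%, and the stated 81.4% power applies to the test that decides the endpoint. The cost is a wording amendment with no change in sample size, visits or data collection. It should be made before database lock and unblinding, as section 2.12 provides.

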### Management of intervention and outcome changes

2.12

The trial will follow the approved protocol. Any change to intervention procedures, eligibility criteria, outcomes, or assessment schedule will require ethics committee approval. Safety-driven immediate changes will be implemented first and reported promptly. All amendments will be documented with rationale, details, and version updates, and the registry and statistical analysis plan will be updated before database lock and unblinding. Protocol deviations will be recorded and reported in the final publication.

## Discussion

3

CID places a substantial burden on both individuals and society. It can markedly impair quality of life and work performance (46) and has been associated with a higher risk of metabolic syndrome (47), hypertension (48), and diabetes (49). Persistent untreated insomnia has also been linked to psychiatric morbidity, particularly depression (50), and may contribute to reduced pain tolerance and impaired immune function (51, 52). In addition, insomnia is often accompanied by anxiety, substance misuse, and other psychological or behavioral problems, including suicidal behavior in severe cases (53, 54).

The conventional acupuncture prescription in this trial includes EX-HN1, EX-HN22, HT7, SP6, BL62, and KI6. It was selected by integrating traditional Chinese medicine theory, clinical experience, and contemporary evidence. In traditional theory, insomnia is related to disturbance of the Heart and Brain and may involve dysfunction of the Liver, Spleen, and Kidney. EX-HN1 and EX-HN22 are commonly used for head-related and sleep-related symptoms; HT7 is used to calm the mind; SP6 regulates yin-yang balance; and BL62/KI6 correspond to the Yangqiao and Yinqiao meridians, which are traditionally linked to sleep–wake regulation.

Systematic reviews of pattern-based acupuncture prescriptions for insomnia have reported that HT7, SP6, EX-HN22, and EX-HN1 are among the commonly selected acupoints in clinical studies (55). A systematic review of randomized controlled trials on primary insomnia has indicated that BL62 and KI6 constitute a frequently used acupoint combination in clinical practice (56). These findings suggest that the present prescription is consistent with the core acupoint-selection patterns observed in previous insomnia studies. In addition, mechanistic studies and reviews indicate that acupuncture at sleep-related points, particularly combinations involving HT7 and SP6, may be associated with modulation of autonomic activity, sleep-related neurotransmitters, neuroendocrine function, and central arousal networks (57, 58).

The stellate ganglion is a major paravertebral sympathetic ganglion and is anatomically relevant to autonomic regulation. Evidence from SGB studies suggests that modulation of this region may influence sympathetic outflow and sleep-related symptoms (59), while experimental studies of electroacupuncture and autonomic neuromodulation indicate that stimulation parameters, including frequency and intensity, can affect sympathetic neural activity (60, 61). In addition, animal and clinical studies of acupuncture for insomnia have reported possible involvement of sleep-related neurochemical pathways, including reduced norepinephrine activity, enhanced GABAergic signaling, and regulation of melatonin secretion (58, 62). These findings provide a mechanistic rationale for incorporating SG acupuncture into CID management. Importantly, ultrasound guidance enables real-time visualization of surrounding anatomical structures and is expected to enhance procedural precision and safety during SG needling. However, because current evidence is indirect and this trial does not measure specific autonomic or neurochemical markers, the pathway linking ultrasound-guided SG acupuncture to sleep improvement remains a biologically plausible hypothesis rather than a confirmed mechanism.

To date, most clinical studies on insomnia have focused either on SG block or on conventional acupuncture alone. Evidence remains limited as to whether SG acupuncture combined with conventional acupuncture can further improve outcomes in CID. This trial therefore evaluates an integrated regimen of ultrasound-guided SG acupuncture plus conventional acupuncture, aiming to combine targeted autonomic modulation with broader symptom regulation. In addition to clinical rating scales, fNIRS will be used to characterize brain functional features, identify disease-related neuroimaging signatures, and compare changes before and after treatment. This multimodal design may improve the objectivity of outcome assessment and help clarify the neurofunctional correlates of acupuncture-related improvement in CID.

The present study is designed as a pragmatic add-on superiority trial in which both groups receive standardized conventional acupuncture, with the treatment group receiving additional ultrasound-guided SG acupuncture. Accordingly, any observed between-group difference reflects the add-on effect of SG acupuncture within this context, rather than the isolated effect of either modality. Several limitations warrant consideration. First, this is a single-center trial with a modest sample size, which may limit generalizability; furthermore, given the absence of published effect-size data for ultrasound-guided SG acupuncture in CID, the sample was powered to detect a clinically meaningful add-on difference in ISI, and smaller neurofunctional effects may be underpowered. Second, the absence of a sham SG acupuncture or para-needling control precludes determination of stellate-ganglion target specificity and prevents full separation of specific physiological effects from nonspecific needling, expectancy, therapist–participant interaction, or ultrasound-related contextual factors. Third, the short follow-up duration (final assessment at week 8) leaves the long-term durability of treatment effects uncertain. Fourth, fNIRS-derived Oxy-Hb signals reflect local cortical hemodynamics rather than direct neural activity, and are subject to confounding by systemic vascular status or CID-related neurovascular alterations; Oxy-Hb changes should therefore not be equated with neural activation or used to draw definitive causal inferences. Relatedly, the verbal fluency task engages prefrontal executive-linguistic networks specifically and may be influenced by semantic memory, linguistic proficiency, and educational background; task-evoked fNIRS responses should thus be interpreted as domain-specific rather than as a generalized index of executive function. Finally, as no universally accepted protocol for SG acupuncture currently exists, the manipulation parameters adopted here are protocol-defined, and optimal stimulation intensity, frequency, and treatment course remain undetermined.

Future research should employ multicenter, sham-controlled designs with larger samples, longer follow-up periods, and objective sleep measurements to confirm and extend these findings.
